
### Procedure

#### Participants

The child welfare project coordinator and child welfare staff will be informed about participant inclusion criteria beforehand to ensure that all participants willing to participate are eligible. They will also receive information on the general study protocol, the intervention, and their tasks in the project. The written informed consent forms provided by the legal guardian will be assessed by the child welfare project coordinator before baseline. The written informed consent forms of the participants will be assessed directly by the study team during baseline assessment.

The total duration for one participant in the trial from screening to the 10-month follow-up is estimated for about 12 months. The individual participant and the respective caregiver will participate in three study visits at the respective child welfare facility (baseline assessment (T0), post-treatment/4-month follow-up assessment (T1), and 10-month follow-up assessment (T2)). All participants will complete self-report questionnaires via the platform REDCap and caregivers (child welfare staff) will complete respective proxy reports via paper–pencil or REDCap, at each assessment time point. At the end of every assessment, the participant will receive a brief feedback on the PTSS, depression, and anxiety scores by the researchers, and a brief written report will be sent to each participant via mail several days after each assessment. The inclusion and exclusion criteria will be assessed at T0. After the inclusion of all participants in the child welfare program, the participants will be randomized to either CBITS or TAU + by sending a list to the randomization center. The outcome of the randomization will be communicated via phone to the child welfare project coordinator and also sent via mail in an official letter. The time span between randomization and the first treatment session should be no longer than 4 weeks. After randomization, the study staff will match a trained therapist to the intervention group and help organize the intervention sessions both with the therapist and the child welfare project coordinator (who will inform participants and caregivers). In each intervention session, the therapist will assess all participants with the CATS-2 ICD-11 PTSD short version via paper–pencil format, collect the questionnaires, and submit them to the study staff. The therapists and participants will complete an alliance rating after the first session and after the last session of the CBITS intervention and the therapists complete a fidelity rating after each CBITS session. The fidelity ratings and CATS-2 symptom monitoring data will be added to an online survey (www. unipark.de) by the therapist after each session.

### Therapists

The therapists who are enrolled in the study will complete their questionnaires via paper–pencil, which will be sent to them via mail. After the therapists are enrolled in the project, they will receive a token for the CBITS web training. Once they completed the web training (confirmation by submitting their certificate to the study staff per email), they will be invited to the 3-day basic training. After the basic training, they will be contacted once there is a child welfare program ready to start the CBITS intervention at their facilities. Lastly, the therapists will be enrolled in a biweekly case consultation group. After all the training and implementation steps, the therapists will receive a certificate to be an approved CBITS therapist.

### Intervention

In the following, both active conditions, CBITS and TAU + , will be described in more detail.

### CBITS

The CBITS program is a skills-based trauma group and individual intervention, which uses evidence-based cognitive-behavioral techniques (e.g., psychoeducation, relaxation, social problem solving, cognitive restructuring, and exposure) and is designed to be delivered by mental health professionals. The theoretical underpinnings are based on cognitive behavioral theory regarding anxiety and trauma. The program consists of ten 45-min group sessions (about six to eight students/participants per group), one to three individual sessions, two child welfare staff psychoeducational sessions, and one parent/caregiver session. For this study, we will specifically train and supervise study therapists to deliver the intervention within child welfare programs. For children in child welfare, CBITS offers several advantages over traditional community-based, individual-level treatment models. First, with its focus on trauma, CBITS has been shown to influence PTSS, depression, anxiety, and school behavior, making it an ideal means to target the diverse problems that children in child welfare face. Second, unlike traditional community mental health services, CBITS is most often provided outside of the clinical setting, making it possible to keep youth in place to receive the program rather than pulling them away for clinic-based treatment. Third, the group format of CBITS broadens the reach of the intervention, making it possible to serve more youth than a traditional individual-based therapy model. From an ethical standpoint, it seems highly appropriate to provide this vulnerable population with a helpful trauma-focused group intervention.

### Implementation of CBITS in the study

Regarding dose (number and length of sessions) and mode (group and individual sessions) of application, this study will closely stick to the evaluated manual and guidelines as there were no known safety issues in the above-described RCTs. In order to implement CBITS, study therapists at the four study centers receive training in CBITS from the CBITS developers at the RAND research cooperation (https://www.rand.org/about.html). We will develop and offer a CBITS training package consisting of a multimedia online training (https://cbitsprogram.org/public-training), an instructor-led 3-day workshop on the intervention, and case consultations on ongoing group interventions via digital conference. After each session, therapists will complete a fidelity checklist (online survey) which will be submitted to the study staff who forward it to the case consultants. The CBITS manual and workbook materials were translated into German in October 2023 and the permission for distribution was granted in November 2023.

### Treatment as usual + 

In the control condition (TAU +), child welfare programs will follow their usual procedures (i.e., routine care of child welfare, referral to medical practitioners and psychotherapists, and handling of prescribed medication, referral to inpatient treatments in case of risk to self and others) which reflects treatment as usual in child welfare programs and the mental health care system in Germany. Additionally, participants in the control condition will receive the same baseline assessment and reporting of screening results as participants in the treatment condition after each assessment. With each report, participants receive a feedback on their scores in the questionnaires and a recommendation (e.g., psychotherapy) that they can follow with guidance from the child welfare staff. Additional treatments will be closely monitored by an adapted version of CAMHSRI-DE [23] in both conditions. After the first follow-up assessment (T_1_; 4 months), all participants in the control condition who still report clinically relevant PTSS (at least 21 points on the CATS-2) and would like to receive the group treatment will be offered participation in CBITS.

### Measures

All self-report measures of the participants and proxy report of the caregivers at the child welfare programs will be assessed via REDCap. Weekly symptom monitoring during CBITS and therapist measures will be assessed via an online survey.

### Primary outcome

The Child and Adolescent Trauma Screen Version 2 (CATS-2) [24] is a questionnaire to screen for potentially traumatic experiences and 20 DSM-5 and ICD-11 symptoms of PTSD in children and adolescents. The measure has been developed by an international expert group led by the Ulm University (applicant and co-applicant of this proposal). The DSM-5 PTSD total score (*α* = 0.89), the ICD-11 PTSD total score (*α* = 0.67), and the ICD-11 CPTSD total score (*α* = 0.83) have proven acceptable to excellent reliability. This CATS-2 version also includes items for measuring ICD-11 Complex PTSD and offers a short version for symptom monitoring during treatment with only 7 items, which will be used in this study for weekly symptom monitoring in the CBITS condition.

### Secondary outcomes

All secondary outcomes will be evaluated at the 4-month and 10-month follow-up. Anxiety and Depression will be measured using the “Revised Child Anxiety and Depression Scale” (RCADS) [25]. The RCADS is a 47-item, youth self-report questionnaire developed to measure DSM-IV relevant symptoms of anxiety disorders (separation anxiety disorder, social phobia, generalized anxiety disorder, panic disorder) as well as symptoms of obsessive–compulsive disorder and depression in children (*α* = 0.73–0.96) [26].

Anger and aggression will be measured via the “Dimensions of Anger Reactions” (DAR-5) [28] rating scale. It is a self-report measure which assesses anger frequency, intensity, duration, and aggression with five items. It has shown a very good internal reliability (*α* = 0.86) [29].

The KIDSCREEN-10 is a generic questionnaire used to measure health-related quality of life via ten items (*α* = 0.77–0.89) [27].

### Additional measures

Socio-demographic data will be assessed with a 12-item questionnaire including the following demographic information: gender, age, duration in child welfare (overall), duration in current child welfare program, number of different placements, contact to family members, relationship status of parents, educational level, and ethnic and social background.

Therapeutic Alliance will be measured via the “Therapeutic Alliance Scale for Children—Revised” (TASC-r). The questionnaire assesses the working alliance between therapists and participants with 12 items, which has shown excellent reliability for participants (*α* = 0.88–0.91) [30]. To assess the Group Alliance, 12 additional items were created based on the original items adapted to the group setting.

The “Inventory for the Assessment of Negative Effects of Psychotherapy for Children and Adolescents” (Children-INEP) consists of 18 items which assess unwanted side effects of the therapy [31].

### Proxy measures

The following measures will be detailed by the respective caregiver of each participant:

The CATS-2 caregiver version [24] which comprises the same items as the CATS self-report with a reference to the child/adolescent (“has your child…”) will be used to measure proxy reported PTSS. The DSM-5 PTSD total score (*α* = 0.91), the ICD-11 PTSD total score (*α* = 0.79), and the ICD-11 CPTSD total score (*α* = 0.87) have proven acceptable to excellent reliability.

Anxiety and depression will be assessed by the RCADS-P (parent-version) [25]. The 47-item inventory measures DSM-IV-relevant symptoms of anxiety disorders (separation anxiety disorder, social phobia, generalized anxiety disorder, panic disorder) as well as symptoms of obsessive–compulsive disorder and depression in children (*α* = 0.73–0.96) [26].

The KIDSCREEN-10 is a generic questionnaire used to measure health-related quality of life via 10 items (*α* = 0.77–0.89) [27]. The parent version will be used and adapted to the caregiver environment.

Affective Reactivity Index-Parent (ARI-P): The ARI-P [25] is a short seven-item instrument to assess irritability in Children via proxy report. The reliability was proven to be good (*α* = 0.89) with an adequate test–retest reliability (ICC = 0.67, 95% CI [0.14, 0.85] [39].

The “Child and Adolescent Mental Health Service Receipt Inventory” (CAMHSRI-DE) [23] is a questionnaire for evaluating the use of medical, psychosocial, and child welfare services, which consists of eight parts assessing the number of additional treatments and medication for the previous months.

The Children-INEP consists of 18 items to assess unwanted side effects of psychotherapy via caregiver report [31].

The “Evidence-Based Practice Attitude Scale” (EBPAS-36, [32]) is a 36-item questionnaire derived from the EBPAS-50. It assesses the attitudes of mental health providers toward the adoption of evidence-based practice, which has been well-validated.

The “Implementation Climate Scale” (ICS, [33]) measures the degree to which the organizational climate is supportive of the evidence-based practice implementation using 18 items. High internal consistency has been confirmed for the total scale (*α* = 0.91) and for the subscales (*α* = 0.81–0.91).

The “Children’s Global Assessment Scale” (CGAS) is an instrument that assesses the level of global functioning. It has proven good inter-rater reliability (*α* = 0.84) and test–retest reliability (*α* = 0.85) [34]).

Socio-demographic data (age, gender, education, work experience, and level of experience regarding the work with traumatized children) will be assessed with a self-created eight-item questionnaire.

To assess serious adverse events (SAEs), the caregivers will complete a standardized checklist. SAEs will be assessed at baseline and follow-ups and as soon as a SAE occurs. If an incident is to be reported, caregivers fill in a detailed report about the SAE and send it to the study center.

Feedback on the study and intervention will be systematically assessed by participants, care givers, and therapists at 4- and 10-month follow-ups.

### Measures for CBITS therapists

Socio-demographic data will be assessed with a 15-item non-standardized questionnaire (therapists’ gender, age, work experience, education, level of experience with trauma and traumatized children in particular).

The TASC-r [30] will be used to assess the working alliance between the therapist and the children with 12 items (*α* = 0.88–0.91). The instrument was translated into German, and 12 additional items adapted to measure the working alliance between the therapist and the group were added. Another 12 items based on the original ones were created that reflect the working alliance perceived out of the therapist’s perspective.

The Treatment Fidelity Checklist will be completed after each CBITS session to assess whether the specific topics were covered. The checklist was translated into German during the trial preparation phase.

### Methods against bias

Random allocation of participants is ensured by the trial design. Stratification by CATS-2 will ensure comparability for PTSS at baseline (T0). The CBITS training will be highly standardized and implemented by certified intervention trainers, treatment fidelity will be ensured by ongoing case consultations and by session checklists. Compensation of the additional training time as part of the regular training and providing access to an otherwise expensive additional clinical training without extra costs will reduce the selectivity of the therapist population under study. The blinding of the participants and therapists is not possible. Study assessors will not be blinded by condition either, but only self-report measures will be used and not clinician-rated interviews. All outcomes on the participant, caregiver, and therapist levels are psychometrically sound and well-established measures. Primary and secondary outcomes are determined in the study protocol to avoid selective reporting (reporting bias/publication bias). Data records will be kept as up-to-date as possible by means of online symptom monitoring and documentation of treatment sessions. All available follow-up data will be included in the final analyses, thus investigating an intention to treat (ITT) population of participants. The mixed model analysis will take missing data and different numbers of reassessments per participant into account. The trial is preregistered at https://clinicaltrials.gov/, and its results will be published irrespectively of significant results to avoid publication bias. The publication of results will be in line with the CONSORT guidelines.

Important protocol modifications will be communicated to trial registries, journals, regulators, funders, advisory board, and DSMB right away via e-mail and conference calls. Trial participants will be informed by letters.

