**Methods:**

In a randomized controlled trial (RCT) involving *N* = 90 children and adolescents, we will compare CBITS with TAU + . Participants between 8 and 16 years, reporting at least one traumatic event and moderate posttraumatic stress symptoms (PTSS), will be randomized within their child welfare institution to either one of the conditions using a CATS-2 severity-stratified block randomization. Assessments will take place at baseline, as well as 4 months and 10 months after baseline. The primary outcome is the severity of PTSS after 4 months. Secondary outcomes are depression, anxiety, irritability/anger, quality of life, and global functioning level.

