### Strengths and limitations

This study has several strengths: (1) By recruiting participants in several different child welfare programs in four different regions in Germany, we will endeavor to recruit a sample that is as representative as possible. (2) The project is aware of the challenges in the child welfare programs (e.g., staff turnover) and will seek to determine the facilities’ readiness to collaborate with mental health services. (3) By randomizing the participants within the child welfare programs and using the control condition TAU + where we document all (mental) health care offers to the participants, we aim to furnish reliable evidence of the actual care for children and adolescents cared for by the child welfare system in Germany. (4) This study claims a high external validity that represents the natural mental health and child welfare context in which children and adolescents in Germany normally reside. (5) The mixed-methods approach on assessment of feedback to the intervention by participants and therapists will allow us a high level of participant involvement.

Possible limitations to the trial are as follows: (1) Some measures will have to be translated to German and are therefore not validated in this language version. (2) The assessment only includes self-report questionnaires and no clinical interviews to ensure a high feasibility of the trial. We will not, therefore, be able to report on clinical diagnoses. (3) We believe that the child welfare programs participating in the trial will show a high motivation to improve mental health care for traumatized children and adolescents who cannot live with their (biological) parents that is probably beyond average. Additionally, therapists willing to participate may be particularly interested in providing EBTs, which could result in a selection bias.

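### The protocol offsets unblinded assessment by saying that only self-report is used, but global functioning (CGAS) is rated only by caregivers who know about the CBITS sessions

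*Protocol article*

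**What the plan says.** Methods against bias in the protocol article says that participants and therapists cannot be blinded, and continues: "Study assessors will not be blinded by condition either, but only self-report measures will be used and not clinician-rated interviews". Strengths and limitations describes the measurement the same way: "The assessment only includes self-report questionnaires and no clinical interviews to ensure a high feasibility of the trial".

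The Proxy measures section opens with "The following measures will be detailed by the respective caregiver of each participant". The list that follows includes caregiver versions of CATS-2, RCADS and KIDSCREEN-10. It also includes ARI-P, which "is a short seven-item instrument to assess irritability in Children via proxy report", and CGAS, which "is an instrument that assesses the level of global functioning".

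The Methods paragraph of the abstract gives functioning formal status: "Secondary outcomes are depression, anxiety, irritability/anger, quality of life, and global functioning level". Under Aims and hypotheses, H2b expects CBITS to be superior on functional impairment, among other outcomes, and the secondary hypotheses are declared exploratory.

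The participant part of the Procedure section identifies the caregivers as child welfare staff. The project coordinator receives the allocation by phone, helps to organise the CBITS sessions and informs participants and caregivers about them. The CBITS section adds that the program contains "two child welfare staff psychoeducational sessions, and one parent/caregiver session".

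**The concern.** The article uses self-report as its answer to unblinded assessment. If the statement were accurate, no outcome would depend on the judgement of an unblinded observer. For functioning the statement is wrong: the score is an observer's rating, and the observer is likely to know which children are in CBITS.

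A reader who relies on the bias section would take a positive H2b result on functioning to have a protection that the design does not give it. The rater's expectation could contribute to the difference, and no child-reported functioning score is named against which to check it.

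**Working it through.** No arithmetic applies: the point concerns who supplies each score. The table sets the abstract's outcomes against the instruments named under Primary outcome, Secondary outcomes and Proxy measures.

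| Outcome | Child self-report | Caregiver form |
|---|---|---|
| PTSS (primary) | CATS-2 | CATS-2 caregiver version |
| Depression | RCADS | RCADS-P |
| Anxiety | RCADS | RCADS-P |
| Irritability/anger | DAR-5 | ARI-P |
| Quality of life | KIDSCREEN-10 | adapted parent version |
| Global functioning | none named | CGAS |

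1. Of the five secondary outcomes in the abstract, four have a named self-report form and one, global functioning, has none.
2. The article itself treats CGAS as an observer rating: it sits under Proxy measures and is given an inter-rater reliability.
3. The Statistical analysis section specifies the primary analysis on the CATS-2 self-report, so the self-report statement is true for H1.
4. On blinding of the caregiver raters, Methods against bias is silent; it covers participants, therapists and study assessors. The Procedure section shows that caregivers are told about the sessions. Randomization is within each child welfare program, so staff of one facility can be looking after children from both arms.
5. On rater continuity, the article says only that the respective caregiver completes the forms. It does not say whether the same person rates a child at T0 and T1.

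The only planned between-group effect, d = 0.4 in the Sample size section, is for CATS-2. No effect is planned for functioning, so there is no figure against which to scale a possible bias in CGAS.

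**The case against.** The strongest reply is that self-report is loose wording for questionnaire as opposed to clinician interview. On that reading the sentence says only that unblinded study personnel do not rate outcomes, which remains true of CGAS and ARI-P. The same section goes on to mention caregiver-level outcomes, and the Measures and Proxy measures sections disclose the proxy reports openly. This stands as an account of what was probably meant. It does not rescue the sentence as a bias argument, because a form filled in by an informed caregiver is still an unblinded observer rating.

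A second reply also stands: the children are unblinded too, so their self-reports are not free of expectation. The point is therefore not that self-report is clean and proxy report is not. It is that the article claims one kind of source and uses another for functioning.

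A reader might infer more than the documents support:

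- **That the raters are themselves treated in one arm.** CBITS includes staff and caregiver sessions, so a rater may have attended. No section says that the caregiver rating a given child does so, and with randomization within programs anything learned there could reach raters of children in either arm.
- **That irritability lacks self-report cover.** The outcome is the single construct irritability/anger, and DAR-5 is its self-report measure under Secondary outcomes. ARI-P is an additional proxy.
- **That staff turnover makes the raters differ between visits.** Turnover is mentioned as a challenge for the programs. Nothing says that raters change, or that they would change more in one arm.
- **That the bias is a stated share of the treatment effect.** Any such figure would rest on an assumed rater shift and on a d planned for a different outcome.

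**Conclusion.** The contradiction is real and narrow. Two statements in the article describe a safeguard that the design does not have for global functioning, one of the five secondary outcomes in the abstract and part of H2b. ARI-P and the caregiver versions are also proxy ratings, but their outcomes have child-reported forms beside them.

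The severity is low. The primary outcome, H1 and the sample size are unaffected, and no confirmatory claim on functioning is planned. The size of any bias in CGAS cannot be derived from the article.

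This conclusion assumes that caregivers who are told about the sessions know which children attend them, which the Procedure section makes hard to avoid. It also assumes that the SPIRIT table, which is not available in the text at hand, names no further functioning measure.

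**What to change.** - **Wording.** In Methods against bias and in Strengths and limitations, replace the self-report statement with one saying that CGAS, ARI-P and the caregiver versions are unblinded proxy ratings.
- **Basis for the secondary hypotheses.** State that H2a and the quality-of-life part of H2b are judged on the child forms (RCADS, DAR-5, KIDSCREEN-10). The Secondary outcomes section already lists these, so this makes the existing structure explicit. State that the exploratory H2b result on functioning rests on an unblinded proxy rating and is supportive only.
- **Conduct.** Have the same caregiver rate a child at T0 and T1 where possible. Record who rated, and whether that person attended a CBITS staff or caregiver session.
- **Analysis.** Do not base a conclusion on the subset of children whose rater stayed the same, because that selects on an event after randomization. If such a comparison is shown, label it descriptive.

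The cost is edited wording, two extra data fields and a slightly weaker claim on functioning. No additional assessor is needed.
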